# Effect of a home-based exercise program on functional mobility and quality of life in elderly people: protocol of a single-blind, randomized controlled trial

**DOI:** 10.1186/s13063-018-3061-1

**Published:** 2018-12-12

**Keywords:** Aged, Motor activity, Quality of life, Community

## Abstract

**Background:**

Elderly people have high rates of functional decline, which compromises independence, self-confidence, and quality of life (QoL). Physical exercise leads to significant improvements in strength, balance, functional mobility, and QoL, but there is still reduced access to this therapeutic strategy due to difficulties in locomotion to training centers or lack of adaptation to the exercise environment.

**Methods/design:**

The purpose of this clinical trial will be to verify the effect of a progressive and semi-supervised, home-based exercise program on the functional mobility, and in the QoL of sedentary elderly people. This is a protocol of a consecutive, single-center, single-blind, and randomized controlled trial. The design, conduct, and report follows the SPIRIT (Standard Protocol Items: Recommendations for Interventional Trials) guidelines. Sedentary elderly people will be enrolled, and randomly allocated into two groups. The intervention group will perform exercises in their own home and the control group will not perform exercises. The evaluations will occur at study enrollment and after 3 months of intervention, and will be performed using the functional mobility Timed Up & Go (TUG) test and sociodemographic and QoL questionnaires. In the statistical analysis, comparisons of mean and correlation analyses will be performed. The primary expected outcome is the improvement in functional mobility verified through the TUG test and the secondary outcome is the improvement in QoL verified by the WHOQOL-OLD.

**Discussion:**

The lack of scientific evidence demonstrating the benefits of semi-supervised home exercise on functional mobility and QoL in elderly people represents an obstacle to the development of guidelines for clinical practice and for policy-makers. The World Health Organization highlighted the importance of musculoskeletal health programs for elderly people, and the exercise program described in this protocol was designed to be viable, easy to implement, and inexpensive, and could be performed at the home of elderly subjects after receiving only guidelines and follow-up via periodic visits. Based on these facts, we hope that this study will demonstrate that a well-structured, home-based exercise program can be effective in improving functional mobility and QoL of sedentary elderly people, even without constant supervision during exercise.

**Trial registration:**

Registro Brasileiro de Ensaios Clínicos (ReBEC), Identifier: RBR-3cqzfy. Registered on 2 December 2016.

**Electronic supplementary material:**

The online version of this article (10.1186/s13063-018-3061-1) contains supplementary material, which is available to authorized users.

## Background

Increased life expectancy is associated with biopsychosocial changes that occur naturally with advancing age [1]; among these changes, the decline in functional performance, and fear of falls are some of the factors with the most influence on quality of life (QoL) in elderly people [2, 3]. The growing process of population aging has emerged as a clinical priority in the fields of public health and social assistance policies [4], considering that old age and disability are among the main determinants of the use of public health services [5, 6].

Elderly people in the community have high rates of functional decline and disability, progressively compromising their independence, self-confidence, and QoL. These impairments are intensified by physical inactivity, which is linked to important negative outcomes in the general health of elderly people [7, 8]. Some studies have demonstrated that the implementation of specific physical exercise programs produces significant improvements in muscle strength, balance, and functional mobility of elderly people, even in subjects of more advanced age, and that regular practice of these exercises produces positive effects on the QoL in this population [7, 9, 10].

However, despite scientific evidence showing the benefits of physical exercise in this population, there is still low adherence to this strategy, possibly related to external factors such as difficulties in locomotion or non-adaptation to the environment where the exercises are performed, since the majority of studies use supervised exercise programs performed at physical training centers [11]. A recent study [12] showed that elderly people with a history of falls prefer to participate in exercise programs that can be performed at home or do not require transportation.

Considering that semi-supervised, home-based exercise is a safe, inexpensive, and easy-to-implement therapeutic resource, this study aims to test the hypothesis that the regular practice of a progressive physical exercise program performed at home improves functional mobility and QoL in a population of sedentary elderly individuals. Our hypothesis is that regular practice of semi-supervised and progressive home exercise improves functional mobility and QoL of sedentary community-dwelling elderly subjects. The primary objective of the study is to verify the effect of a progressive and semi-supervised, home-based exercise program on the functional mobility of a population of sedentary elderly persons in the community. The secondary objective is to analyze the effect of a progressive and semi-supervised, home-based exercise program on the QoL of a sedentary elderly population in the community.

## Methods/design

### Study design and setting

The design and conduct of this study follows the guidelines of The Standard Protocol Items “Recommendations for Intervention Trials (SPIRIT) guidelines” [13], according to the flow chart of the study showed in Fig. 1. This is a blind, randomized controlled clinical trial, using a superiority test and a 1:1 allocation ratio. The sample will be of convenience, composed of elderly subjects in a community in the city of Senhor do Bonfim, BA, northeastern region of Brazil. The protocol is reported according to the Standard Protocol Items: Recommendations for Interventional Trials (Fig. 2 SPIRIT diagram and Additional file 1: SPIRIT Checklist).

**Fig. 1 Fig1:**
[figure not shown]
Flow chart of the study

**Fig. 2 Fig2:**
[figure not shown]
Standard Protocol Items: Recommendations for Interventional Trials (SPIRIT) diagram

### Ethical and legal aspects

This study protocol was approved by the Research Ethics Committee of the Bahia School of Medicine and Public Health (Brazil), process no. 39072514.6.0000.5544, and was registered on the website “ensaiosclinicos.gov.br with Identifier: RBR-3cqzfy.” All participants must agree and sign the informed consent form to participate in the study. Removal is permitted at any time without any loss. After the explanatory meeting with all subjects involved in the study, the informed consent will be obtained individually, in a reserved place, by the main investigator and supervising physician.

### Participants and recruitment procedure

The research will be conducted from December 2016 to July 2019, involving elderly people of both sexes, aged over 60 years old, living in the municipality of Senhor do Bonfim, BA, in the northeastern region of Brazil. Recruitment will be consecutive, across the community, from December 2016 to December 2018. Initially, it will take place through the dissemination of the research study in local newspapers, radios, religious centers, meeting groups for the elderly, senior residency, neighborhood associations, and the Third Age Project developed by the Municipal Government. In this announcement will be provided a telephone so interested people will be able to contact the team of researchers.

### Eligibility criteria

The inclusion criteria for the study will be age ≥ 60 years old and not having performed regular exercise for at least 3 months prior to the start of the study. Participants with cognitive deficits will be excluded according to the Portuguese version of the Mental State Mini Exam (MSME) (an illiteracy group ≤ 20, a primary school group ≤ 25, a junior high school group ≤ 26.5, a high school group ≤ 28, and a well-educated group ≤ 29). According to the authors, its application is very good for hospital patients, outpatients, and for the population study, including the elderly [14]. Participants will also be excluded if they have any clinical and/or orthopedic condition that contraindicates the performance of regular physical exercise, identified through a clinical and physiotherapeutic evaluation.

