### Sample size

The sample size was calculated using the WINPEPI (PEPI-for-Windows) [21] software, based on the main hypothesis of the study. According to a relevant study published by Lacroix et al. [8], where a group of health older adult subjects performed unsupervised exercises obtaining a reduction of 0.37 s in TUG execution time when compared to pre and post intervention with duration of 12 weeks. Considering the standard deviation of 0.84 for the IG and 1.02 for the CG observed in the study, with a statistical power of 80% and an alpha error of 5%, 101 participants in each group would be necessary. The sample will be increased by 10% to compensate for possible dropouts, leading to 111 subjects in each group (overall sample = 222 participants).

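### The cognitive exclusion limits for the two highest schooling levels (28 and 29) leave almost no score eligible on a 30-point test, so one lost point can count as a deficit

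*Protocol article*

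**What the plan says.** The Eligibility criteria section of the protocol article sets the purpose and the rule in one sentence. The purpose is this: "Participants with cognitive deficits will be excluded according to the Portuguese version of the Mental State Mini Exam". The limits follow in brackets. For the two lower schooling levels they are "an illiteracy group ≤ 20, a primary school group ≤ 25"; for the three higher levels they are "a junior high school group ≤ 26.5, a high school group ≤ 28, and a well-educated group ≤ 29". Read as written, a score at or below the limit means exclusion as cognitively impaired.

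The section gives no score range, norm, sensitivity or specificity. The only support offered is a remark credited to the authors of reference [14], that "its application is very good for hospital patients, outpatients, and for the population study, including the elderly". That speaks for the instrument, not for these five limits. No other section changes or softens the rule.

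**The concern.** A limit for impairment should sit below the scores that unimpaired people commonly reach. In the two highest schooling groups the printed limits appear to sit at the top of the scale, so the rule would remove people who have no deficit.

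The hypothesis in the Background section is that the programme "improves functional mobility and QoL of sedentary community-dwelling elderly subjects". If the rule is enforced, better-schooled participants are confined to top scorers on the test, which narrows the population to which the result applies and lowers the recruitment yield. The section on quality control and governance has the management committee check that recruits meet the criteria, so the rule is meant to be followed as printed. Should a different rule be used in practice, the published eligibility would not describe the sample.

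**Working it through.** **Inputs from the article (Eligibility criteria):** excluded at or below 20 (illiterate), 25 (primary), 26.5 (junior high), 28 (high school) and 29 (well-educated).

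**Assumption, not in the article:** maximum score 30, whole points.

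The article has no figure of its own to reproduce here. Its one calculation, the sample size, does not use these limits.

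**Step 1. Scores left eligible.** With limit L and maximum 30, the eligible scores are the whole numbers above L.

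| Schooling | Excluded at or below | Eligible |
|---|---|---|
| Illiterate | 20 | 21 to 30 |
| Primary | 25 | 26 to 30 |
| Junior high | 26.5 | 27 to 30 |
| High school | 28 | 29, 30 |
| Well-educated | 29 | 30 only |

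**Step 2. Sensitivity to the assumption.** For a general maximum M in whole points, the number of eligible scores is M − 29 in the well-educated group and M − 28 in the high-school group. With M = 29 nobody well-educated could enter, so the rule itself implies M of at least 30. With M = 30 the counts are 1 and 2. Each extra point on the scale would add one eligible score to each group. If half points were allowed with M = 30, the well-educated group would be eligible at 29.5 and 30, and one full lost point would still exclude.

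**Step 3. The 26.5 limit.** The other four limits are whole numbers. In whole points nobody scores 26.5, whereas a group mean or median can take that value. This is a hint about where the figures came from, and no more than that.

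**Step 4. Illustrative share of intact people excluded.** The article gives no score distribution. Treat the score X of an intact person as binomial: 30 independent points, each gained with probability p. Then:

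- P(X ≤ 29) = 1 − p^30
- P(X ≤ 28) = 1 − p^30 − 30 p^29 (1 − p)

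Example at p = 0.95: p^30 = 0.215, so P(X ≤ 29) = 0.785. The second term is 30 × 0.226 × 0.05 = 0.339, so P(X ≤ 28) = 1 − 0.215 − 0.339 = 0.446.

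| p | Excluded at ≤ 29 | Excluded at ≤ 28 | Excluded at ≤ 26.5 |
|---|---|---|---|
| 0.995 | 14% | 1% | < 0.1% |
| 0.99 | 26% | 4% | < 0.1% |
| 0.98 | 45% | 12% | 0.3% |
| 0.97 | 60% | 23% | 1.2% |
| 0.95 | 79% | 45% | 6.1% |

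The well-educated limit costs a material share over the whole range. The high-school limit does so once p is about 0.98 or lower. The values of p are chosen for illustration, and the model ignores dependence between items and differences by schooling.

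**The case against.** - **Scope.** A reader might infer that all five limits demand near-perfect scores. They do not: on the assumed scale the illiterate and primary groups are eligible from 21 and from 26. The limits are graded by schooling, and the point is confined to the top two. This stands.
- **The 26.5 limit.** A half-point limit works without ambiguity on whole-point scores, since it separates 26 from 27. This stands too: the figure causes no operational error and proves nothing about its source.
- **Size.** A reader might infer that at least half of intact people are excluded in every schooling group. That would need the figures to be medians of unimpaired people, which the article does not say, and it would not follow if they were means. Likewise, one eligible score out of 31 possible scores is a count of values, not of people. Without the schooling mix or any score distribution, the real loss is unknown.
- **Consequence.** A reader might infer a biased treatment effect. The criterion acts before randomization and equally on both future arms, so the comparison between groups is unaffected, as are the primary outcome and the sample-size calculation.
- **Context and timing.** The sample is declared to be one of convenience, no recruitment shortfall is reported, and nothing indicates that staff use another rule. The article appeared on 12 December 2018. The recruitment section ends recruitment that month, while the Trial status section expects it to run to July 2019, so an amendment may reach few participants.

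None of this removes the core. The limits are printed as exclusion limits, and in the top two groups, on the stated scale, they class one lost point (well-educated) or two (high school) as a deficit.

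**Conclusion.** The concern holds for the high-school and well-educated limits. On a 30-point whole-number scale, which is an assumption, only 29 and 30 are eligible in the first group and only 30 in the second. Followed literally, the rule can be expected to exclude people without a deficit, so it does not do what it is stated to do.

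The extent cannot be derived from the article; the binomial range above is illustrative only. That group summary scores were taken as impairment limits is a plausible explanation, to be settled from reference [14]. The damage is to recruitment yield, to generalisability and to accurate reporting of who was eligible. It is worth correcting, but it does not threaten the validity of the randomized comparison.

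**What to change.** 1. Check all five limits, and the direction of the inequality, against reference [14], and state whether they are impairment limits or typical scores by schooling.
2. If they are typical scores, amend the criterion for remaining recruits to the limits which that source supports for impairment, expressed in whole points. No replacement values are proposed here.
3. State the score range of the test and the rule that was actually applied at screening.
4. Report the number screened out on this criterion by schooling level, before and after any change.

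The cost is a source check, a tabulation of the screening log and, if needed, a small eligibility amendment. The downside is that participants enrolled before and after the amendment would have entered under slightly different criteria, which the report should say. If recruitment has already closed, items 1, 3 and 4 still apply as reporting corrections.

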### Randomization and allocation concealment

All subjects involved in the study, before randomization, will participate in groups of 12 elderly in a 40-min talk with explanations on the evaluation and intervention procedures and will receive educational leaflets containing guidelines on healthy habits related to food, hydration, and sleep hygiene. The subjects in the IG will be informed that they will follow the guidelines of healthy habits of life and a program of home-based physical exercise. For this program, they will participate in theoretical-practical training concerning adequate accomplishment of the exercises and will receive a booklet, developed by the researchers, that contains illustrative and written guidelines on the method of performing the exercises, and a diary to register the frequency of exercise on a weekly basis.

After the explanatory meeting with all subjects, the main investigator will enroll the subjects of the study and request the randomization. A researcher from the same department, not involved in the trial, will prepare the group allocation after explanatory meeting and baseline assessment. Randomization will be computer based and carried out at a 1:1 ratio according to a random sequence generated by the Research Randomizer (https://www.randomizer.org/), generating two groups, control group (CG) and intervention group (IG: semi-supervised, home-based exercise program). Consecutively numbered, sealed, opaque envelopes containing group allocation will be prepared by the same researcher not involved in the trial. The concealed envelopes will be securely stored and will be opened in sequence to reveal group allocation (CG or IG).

The researchers, after making sure that the participants will be able to properly perform all the proposed exercises, will guide the family members to help the participants and stimulate their practice. Any change in the physical or mental condition of the participants should be communicated by telephone to the research team. Participants in the CG will be informed that they should only continue their daily living activities and follow the guidelines of healthy living habits.

### Clinical evaluation

A previously trained physician and physiotherapist will perform all evaluations. Participants will receive standard verbal instructions on the procedures and will be evaluated individually in an appropriate room. Evaluations will be conducted before and after the intervention period. A clinical evaluation, physical examination, and evaluation of functional mobility, and physical activity levels, and QoL will be performed and socioeconomic, demographic, anthropometric, and self-referenced morbidity data will be collected according the schedule for data collection and outcome measurement (Table 1).

**Table 1 Tab1:**
[figure not shown]
The schedule for data collection and outcome measurement

*CG* control group, *IG* intervention group, *CHAMPS* Physical Activity Questionnaire for Older Adults

Weight will be measured while wearing light clothing and without shoes, after emptying of the bladder, using a digital scale to the nearest 100 g. Height will be measured without shoes, with a stadiometer to the nearest 0.5 cm (model 200/5; Welmy Industria e Comercio Ltda, Sao Paulo, Brazil). Body Mass Index (BMI) will be calculated by dividing weight (kg) by the square of height (m) [15].

Functional mobility will be evaluated by the Timed Up & Go (TUG) test. This test measures, in seconds, the time taken by an subject to stand up from a standard arm chair (seat of the chair with height of 46 cm and arms with 65 cm of height), walk a distance of 3 m, at a comfortable and safe pace, turn, walk back to the chair, and sit down again. The subject wears his regular footwear and uses his customary walking aid (none, cane, or walker). Three tests will be performed with each subject in a 1-min interval, with the best performance being chosen as the final measure [16].

According to the test, an execution time of less than 10 s suggests totally free and independent individuals. Individuals who perform the test between 10 and 19 s are considered independent, and those who perform the test in 20 to 29 s are in the so-called “grey zone,” that is, demonstrating limited functional capacity and difficulties in tasks of daily living. Those who perform the test in 30 s or more tend to be totally dependent for many basic and instrumental activities of daily living [16].

The measurement process of physical activity levels requires the use of reliable and valid assessment tools. One of the most common assessment tools is questionnaires, with the advantage of low cost and easy administration. To evaluate the levels of physical activity among the elderly subjects involved in this study, a well-known efficacy instrument called the Physical Activity Questionnaire for Older Adults (CHAMPS) will be used. The CHAMPS is one of the first physical activity questionnaires for older adults designed specifically for use in evaluating interventions that primarily aim to increase levels of physical activity in older adults. According to the authors, the CHAMPS measure may be useful for evaluating the effectiveness of programs aimed at increasing levels of physical activity in older adults [17].

The CHAMPS assesses the level of physical activity in older adults (> 60 years and/or) taking into consideration caloric expenditure and frequency of the activities performed. This instrument is composed of 41 questions in which the answer is “yes” or “no.” After responding “yes,” the answer specifies the frequency of days and hours per week that the activity was performed within the last 4 weeks. The types of activities assessed by CHAMPS are activities of daily living at home, exercise, and recreational activities [17, 18]. In this study, the CHAMPS will be applied at the baseline moment of data collection and at the end of the execution of the home exercise program, according to the proposed protocol.

Quality of life will be evaluated using the World Health Organization Quality of Life Group for Older Adults (WHOQOL-OLD) questionnaire, which contains six facets of four items each, evaluated by a Likert scale (1 to 5 points): Facet I **–** “Sensory Function”; Facet II **–** “Autonomy”; Facet III **–** “Past, Present, and Future Activities”; Facet IV **–** “Social Participation”; Facet V **–** “Death and Dying”; Facet VI **–** “Intimacy.” Each of the facets has four items; thus, for all facets the score of the possible values ranges from 4 to 20, and the scores of these six facets or the values of the 24 items can be combined to produce a “global” score of the QoL [19].

